**Fig. 2 Fig2:**
[figure not shown]
Participant timeline as per SPIRIT guideline

Primary and secondary outcomes will be measured three months (84 days) after the videocall in which the tablet training is provided to the person with dementia. Semi-structured interviews (SSIs) with selected dyads will take place within 3 months (91 days) of the videocall in which the tablet training is provided to the person with dementia. Cost-effectiveness of the FindMyApps intervention will also be assessed as part of this study. Use of health and social care will be assessed on a monthly basis (after 42 and 70 days) during the three-month intervention period. Data regarding use of the tablet, which supports the process evaluation, will also be measured at intermediate points (after 42 and 70 days), as well as continuously in the experimental group by analytics software.

### Sample size

Two pilot randomized controlled trials preceded this definitive trial, both of comparable design with comparable outcome measures [36, 37]. Values of partial eta squared with respect to primary outcomes measured with instruments which will also be used in the present study, were found to range from 0.01 (MSPP) to 0.38 (PAL). These correspond to small to large effect sizes, respectively, when compared to Cohen’s suggested benchmarks [38]. Previous evaluations of interventions implemented in the Netherlands to improve social health in dementia have also found moderate to large effect sizes, with respect to similar outcome measures [39, 40]. Whilst both pilot studies also revealed small between group differences with respect to a number of outcomes, this trial will not be powered to detect small effects of the intervention. We do not believe that small effects of the intervention – even if statistically significant – would be ‘clinically’ significant. We therefore do not feel that we could justify the additional use of public funds to conduct the trial in such a way as to have adequate power to detect small effects of the intervention.

Effects of the intervention on primary outcomes for the primary participants (social participation and self-management) will be tested using MANCOVA. An a priori power calculation was conducted using the software G*Power, version 3.1, for main effects MANOVA, assuming two dependent variables, two groups, alpha = 0.05 and power = 0.8, and a moderate overall effect. The total required sample size would be *n* = 158. This is an overestimate of the required sample size to achieve a power of 0.8 because the inclusion of covariates in the MANCOVA is expected to increase the statistical power of the test compared to MANOVA (thereby reducing the required sample size for the desired power of 0.8).

In the two pilot trials evaluating the FindMyApps intervention, drop-out rates were 12 and 37% between baseline and three-month follow-up [36, 37]. Other randomized controlled trials evaluating the effectiveness of technology for social health in dementia that we are aware of, have experienced drop-out rates from baseline to three-month follow-up of around 20% [41, 42]. We are also aware of recently-conducted RCTs involving community-dwelling participants with dementia in the Netherlands, one of which reported a drop-out rate of 12% after three months and the other reported a dropout rate of 35% after six months [39, 43]. A recent review of web-based brain health interventions designed for healthy adult participants identified trials which reported drop-out after various periods of time, with rates ranging from 2 to 52% [44]. With respect to the present study, allowing for a dropout of 20% in the calculation of statistical power for a per protocol analysis, 94 participants per group would have to be randomized. However, this number may be lower in practice if the actual dropout rate is less than 20%. This is a reasonable expectation given that both the FindMyApps intervention and the trial procedure have been improved based on the results from the pilot studies. In the first instance we will therefore aim to randomize 75 participants per group. We will review this target based on the actual drop-out rate as the trial progresses.

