### Allocation

Participants will be randomly assigned to either the FindMyApps (experimental) or usual care (control) arm. Randomization will be performed via Castor EDC, following a variable blocked randomization method, with a target of 1:1 allocation and randomly selected block sizes of 4 or 6. Group allocation will be stratified on the basis of diagnosis (MCI or dementia) and any prior experience with the use of a tablet (participant self-report; ‘Yes’ or ‘No’).

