### Data management and analysis

Quantitative demographic data and data pertaining to participants who withdrew from the study after randomization (dropouts) will be analyzed with descriptive statistics. Differences between the trial arms will be tested with appropriate (non) parametric differences tests (Chi2, Mann-Whitney U, Student’s t-test).

For the effect evaluation, differences between the groups on the primary outcome measures will be tested by MANCOVA on post-test data, including baseline data and potential confounders as covariates in the analysis. Diagnosis (MCI or dementia) will be included as a fixed factor. We will carry out both intention-to-treat and ‘per protocol’ analyses following completion of data collection. Where we encounter missing data as a result of participants withdrawing from the study, we will use appropriate methods to impute that data and perform sensitivity analyses accordingly. Analyses will be conducted using SPSS. We will primarily report effect sizes with calculated 95% confidence intervals, however we will also report *p*-values. We will use 2-tailed p-values with an alpha of 0.05.

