## Discussion

Two pilot RCTs helped to establish a protocol for the evaluation of the feasibility and effectiveness of the FindMyApps intervention. Although the protocol for the present study was amended in light of the 2020 coronavirus pandemic, this study goes further than any previous study of the FindMyApps intervention in four important ways.

First, by conducting the effect evaluation in a larger study (n_tot_ = 150; 75 experimental group, 75 control group), we hope to conduct this trial with a reasonable power to detect medium effect sizes (MANCOVA: η^2^ = 0.06; power 0.80, alpha = 0.05), to be able to conduct analyses from which robust conclusions about the intervention’s effectiveness for the target group of community dwelling people living with MCI/dementia and their caregiver can be drawn. A frequent criticism of eHealth or digital health interventions has been a lack of scrutiny in the context of high quality RCTs [11]. This trial will also contribute to the growing pool of RCTs in the field of eHealth and digital health, which is needed for the field to mature.

Second, by means of a process evaluation to review implementation of the FindMyApps intervention among a larger group of participants, we aim to leverage better insight into the contextual, implementation and mechanisms of impact factors that may influence implementation and adoption of FindMyApps, and the study outcomes. This will better inform further evaluation and implementation of FindMyApps compared with existing research.

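### The 94 per group said to allow for 20% drop-out does not follow from the protocol's only stated requirement of 158, which gives 99 per group

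*Protocol article*

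**What the plan says.** All the figures are in the Protocol article, mainly under Sample size.

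- The power calculation is for a main-effects MANOVA, "assuming two dependent variables, two groups, alpha = 0.05 and power = 0.8, and a moderate overall effect". Its result is "The total required sample size would be *n* = 158", which is 79 per group.
- The next sentence qualifies that result, pointing to a gain in power: "This is an overestimate of the required sample size to achieve a power of 0.8 because the inclusion of covariates in the MANCOVA is expected". No smaller number and no covariate R² is given.
- The drop-out step gives the number to randomize: "allowing for a dropout of 20% in the calculation of statistical power for a per protocol analysis, 94 participants per group would have to be".
- The first recruitment target is then set at 75 per group, in the expectation that drop-out may stay below 20%. The section adds: "We will review this target based on the actual drop-out rate as the trial progresses".
- The Discussion attaches "MANCOVA: η^2^ = 0.06; power 0.80, alpha = 0.05" to a total of 150.

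The base from which 94 was inflated is not stated anywhere.

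**The concern.** A reader takes 158 as the number to be analysed and 94 per group as that number grossed up for 20% loss. The division does not give 94. Either the inflation is wrong, or it started from a different base that is not disclosed.

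The figure matters because it is the only drop-out-adjusted number in the protocol, and the protocol promises to revisit the recruitment target in the light of actual drop-out. Drop-out near 20% is realistic on the protocol's own evidence: 12% and 37% in the two pilot trials, and around 20% in comparable trials. If the target were raised to 94 per group at 20% drop-out, the trial would report that it had allowed for drop-out while ending with about 150 completers, 8 fewer than the 158 it calculated.

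**Working it through.** **Inputs.** Two dependent variables, two groups, alpha 0.05, power 0.80 and a total of 158 (Sample size); 1:1 allocation (Allocation); 20% drop-out and 94 per group (Sample size); η² = 0.06 (Discussion). Sample size calls the effect only moderate, without a figure. I assume f² = 0.0625 because it reproduces 158, and use η² = 0.06, that is f² = 0.06/0.94 = 0.0638, as the alternative.

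**1. The protocol's base figure.** For a global MANOVA with two groups and two responses, power comes from a noncentral F with 2 and N − 3 degrees of freedom and noncentrality N × f².

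- f² = 0.0625: the smallest N reaching 0.80 is 158, with power 0.802. The stated 158 reproduces.
- η² = 0.06: the smallest N is 154, with power 0.800.

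**2. Inflation for drop-out.** The number to randomize is N/(1 − d).

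- 158/0.80 = 197.5, so 198 in total or 99 per group. The stated 94 per group (188) is 10 dyads lower.
- 154/0.80 = 192.5, so 97 per group. The Discussion's effect size does not yield 94 either.

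**3. What 94 per group delivers.**

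- Completers at 20% drop-out: 188 × 0.80 = 150.4, about 150.
- Largest drop-out that still leaves 158: 1 − 158/188 = 16.0%.

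**4. Where 94 may come from.**

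- 75/0.80 = 93.75, which rounds up to 94. This inflates a base of 150.
- 79 × 1.2 = 94.8, which rounds up to 95. This multiplies by 1.2 where it should divide by 0.8.

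The first route matches exactly, but the protocol states neither.

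**5. Power at 150 completers, MANOVA as reported.**

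| Effect size | N = 150 | N = 158 |
|---|---|---|
| f² = 0.0625 | 0.780 | 0.802 |
| η² = 0.06 | 0.789 | 0.811 |

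**6. Power at 150 completers with covariates.** The noncentrality becomes N × f²/(1 − R²), and the denominator degrees of freedom fall by the number of covariates. R² and the number of covariates (three) are my assumptions, since the protocol gives neither. With f² = 0.0625:

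| Assumed R² | Power at N = 150 |
|---|---|
| 0 | 0.779 |
| 0.05 | 0.801 |
| 0.10 | 0.823 |
| 0.30 | 0.911 |

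The smallest R² that gives 0.80 is about 0.048, and this hardly changes between none and eight covariates.

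**The case against.** The best defence is that 158 was never meant as the final requirement. The protocol calls it an overestimate for the test actually planned, a MANCOVA on post-test data with baseline values and potential confounders as covariates. The Discussion then links a MANCOVA power of 0.80 to a total of 150, and 150 inflated for 20% drop-out is 188, exactly 94 per group. On that reading the division is right, and what is missing is the step from 158 to 150.

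Much of this stands. The reading is plausible, and the R² needed to support it is small when baseline scores are among the covariates. But the reduced number and the R² behind it are not in the text, and the Discussion's 150 is the number randomized, not the number of completers. The defence explains how 94 could have arisen. It does not make 94 follow from the inputs printed.

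A reader might go further and infer that the trial will miss its power of 0.80. The documents do not support that, because the 0.78 belongs to a MANOVA without covariates, which is not the planned test. A reader might also take 94 as the formal fallback target or the fixed reference for the later review. The section gives it neither role; it says only that the target of 75 per group will be reviewed.

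**Conclusion.** The figure is wrong as written or rests on an undisclosed base. From 158 and 20% drop-out the number is 99 per group, not 94. The gap is 10 randomized dyads, or about 8 completers at 20% drop-out. This part depends only on the protocol's own numbers.

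The consequence is small: about 2 points of power on the reported MANOVA, 0.80 falling to 0.78 under the assumed f² of 0.0625, or to 0.79 at η² = 0.06. No loss is demonstrated for the planned MANCOVA, where an R² of about 0.05 (assumed, not given in the protocol) closes the gap. No test or estimand changes. I rate it minor, but it should be corrected, because the protocol intends to revisit recruitment in the light of drop-out and a reader cannot tell which analysed number it is protecting.

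**What to change.** Restate the figure under Sample size in one of three ways:

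- (a) If 158 is the base, give 99 per group (158/0.80 = 197.5, so 198 in total).
- (b) Keep 94 per group, and state that it preserves 158 completers up to about 16% drop-out, or that at 20% drop-out it leaves about 150 completers with MANOVA power of about 0.78.
- (c) If 150 analysed was intended as the MANCOVA requirement, say so, give the covariate R² assumed (about 0.05 is enough at f² = 0.0625), and show 150/0.80 = 187.5, so 188.

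Then use the base so stated, divided by (1 − observed drop-out), when the recruitment target is reviewed.

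The cost is one or two sentences. None of the options changes the initial target of 75 per group, so the correction enrols nobody extra. If (a) is chosen and drop-out does reach 20%, the review would point to 198 instead of 188, and the sponsor can weigh those 10 dyads then.

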### Recruitment

Recruitment will take place nationally throughout the Netherlands.

Participants will be recruited: via national networks of Meeting Centers, Alzheimer Cafes, memory clinics and day centers; through the Alzheimer Centre and Centre for Elderly Care Medicine of the Vrije Universiteit Medical Centre (VUmc) in Amsterdam; and through the website and social media platforms of the study, Alzheimer Nederland and other stakeholders.

The center for geriatric medicine (COGA) and Alzheimer Center of Amsterdam UMC, location VUmc, will support recruitment from their patient populations, by providing access to existing databases of eligible patients with an interest in research and by informing newly diagnosed patients who may be eligible for the study.

Interested participants will also be able to self-refer for eligibility screening via online channels, including the project website, the website of Dutch national dementia association Alzheimer Nederland and the websites of various smaller interest groups, organizations and charities.

National recruitment will continue until the required sample size has been met. It is expected that the recruitment period will extend over 23 months (100 weeks). In a previous pilot study, which was mainly conducted in two regions in the West and East of the Netherlands, 59 dyads were recruited over 12 months. Eighteen dyads were recruited in the final 12 weeks of the inclusion period for the pilot study, once relationships with referrers and public awareness were better established. The present national study can build on the network of referrers that was developed in this pilot study. Assuming at least the same average rate of inclusions for the duration of this study, and taking into account the larger recruitment area, this should allow for sufficient inclusions in the intended period.

### Allocation

Participants will be randomly assigned to either the FindMyApps (experimental) or usual care (control) arm. Randomization will be performed via Castor EDC, following a variable blocked randomization method, with a target of 1:1 allocation and randomly selected block sizes of 4 or 6. Group allocation will be stratified on the basis of diagnosis (MCI or dementia) and any prior experience with the use of a tablet (participant self-report; ‘Yes’ or ‘No’).

### Blinding

Due to the nature of the intervention, it is not possible to blind study participants, caregivers or interviewers to the allocation status of participants and outcome measures in the study are based on participant and caregiver self-report. Efforts will be made by researchers to minimize the awareness of participants in the control group of the nature of the FindMyApps intervention. In communication by researchers with study participants, the emphasis will be placed on the evaluation of the effect of the use of tablets and apps, rather than on the evaluation of FindMyApps per se. Through these measures, it is probable that participants will remain blind to the hypotheses being tested.

Data analysis will be conducted by researchers blinded to the group identities. Independent researchers with a data management role will remove or replace identifiers from the datasets prior to analysis, namely the participant codes and the labels of the group variable.

### Data collection methods

Data pertaining to outcomes reported by people with dementia will be collected from the participant by questionnaires filled in electronically by trained researchers during an interview by videocall using the software Microsoft Teams.

Data pertaining to caregiver-reported outcomes will be collected from caregivers by self-report questionnaires, sent by email with data input directly into the study database. Where this is not possible, data will be collected by the researcher by means of an interview by phone and entered by the researcher into the electronic database.

All instruments used in this study have been validated in previous psychosocial studies. The majority were used in a pilot trial evaluating the FindMyApps intervention and proved to be usable for participants.

#### Primary outcome measures

Few instruments exist, which specifically measure self-management as a component of social health and are relevant to the target group of community-dwelling people with dementia [45]. To minimize burden on participants, efficient use of fewer instruments is desirable. Self-management as a facet of good social health in dementia has been defined as the extent to which a person is able to exert control over their daily life to engage in meaningful daily activities [6]. In this definitive trial, participants’ self-management will be assessed using the Adult Social Care Outcomes Toolkit questionnaire (ASCOT). and the Pleasurable Activities List (PAL). ASCOT consists of 9 items, with each item representing one of the following domains: control over daily life, personal cleanliness and comfort, food and drink, personal safety, social participation and involvement, occupation, accommodation cleanliness and comfort and dignity [46]. Two items represent the dignity domain. Levels in each domain define the level of need: ideal state, no needs, some needs, and high-level needs. The test-retest reliability of the Dutch translation of the ASCOT is good (intra-class correlation = 0.71; 94% CI: 0.60–0.78). The short PAL used in this study consists of 19 items, each rated on a five-point rating scale ranging from 1 = “not at all” to 5 = “very frequently” with respect to how often the participant has engaged in a given activity during the preceding month. Items 1, 3 and 6 from the ASCOT questionnaire are particularly relevant to self-management, as they represent domains of control over daily life, ability to eat and drink, and general occupational function respectively. The PAL describes the frequency with which participants engage in a range of pleasurable and meaningful daily activities. Collectively the extent to which participants self-manage their daily lives is described by these instruments.

Participants’ social participation will be primarily assessed by the Maastricht Social Participation Profile (MSPP) [47] Supplementary information regarding social activity will be collected using The Older Persons and Informal Caregivers Survey Minimum DataSet (TOPICS-MDS) social activities questions [48] and the short PAL (items 4–6, 8–10, 15, 17 and 19) [28, 49]. The MSPP measures actual social participation on four indices: consumptive participation (nine items), which is characterized as benefiting from society (for example taking a course or visiting a restaurant); formal social participation (two items), which is characterized as contributing to society (participation in clubs and volunteer work); and two sub-domains (acquaintances and family) of informal social participation (nine items), which is characterized as contributing to society, receiving or both. Intraclass correlation coefficients per domain (range 0.63–0.83) are good. The TOPICS-MDS and selected items from the PAL represent a broad range of social activities, which will provide rich supplementary information to that provided by the MSPP.

Caregivers’ sense of competence will be measured with the Short Sense of Competence Scale (SSCQ), a 7-item questionnaire, with answers given on a Likert scale from 1 (strongly agree) to 5 (strongly disagree) [50]. The calculated total score (sum of all answer scores) is a reliable measure of sense of competence (Cronbach’s alpha = 0.76).

#### Secondary outcome measures

Participants’ experienced autonomy will be measured by the Experienced Autonomy questionnaire (EA) [51]. Quality of life will be assessed by the Dementia Quality of Life instrument (DQoL) [52] and the EQ-5D-5L [53, 54]. The EQ-5D-5L is not specific to dementia but is a recognized international standard in health-related quality of life assessment and will allow for comparison of the results of this cost-effectiveness analysis with other studies. The nature and severity of neuropsychiatric symptoms experienced by people with dementia will be measured by the Neuropsychiatric Inventory Questionnaire (NPI-Q) [55]. The neuropsychiatric inventory has been chosen to compliment the assessment of social participation, as behavior and mood disturbances are known to be associated with reduced social participation [56]. Moreover, previous studies have demonstrated the potential for interventions aimed at improving social health to have a positive effect on reducing neuropsychiatric symptoms [39, 57].

Caregivers’ attitudes to people with dementia will be measured by the Dutch version of the Approaches to Dementia Questionnaire (ADQ) [58]. The ADQ has been chosen on the basis of its use in stigma research to evaluate whether the pedagogical relationship between caregiver and person with dementia impacts upon the caregiver’s perception of the person receiving care. This hypothesis emerged from qualitative research undertaken as part of an earlier pilot evaluation of FindMyApps [59]. Caregivers’ experience of providing care will be measured with the Positive Experience Scale (PES) [60]. Caregivers’ quality of life will be measured with the Dutch version of the EQ-5D-5L.

Data relating to health and social care costs will be collected from participants at one, two and three months by a retrospective questionnaire adapted from the Dutch version of the RUD-Lite instrument [61]. The adaptations focus the instrument on the most important costs associated with the target group of the present study from a societal perspective. The adapted questionnaire therefore reduces the potential burden on study participants, with the expectation of improving response rates and the amount of detail given, at the expense of negligibly valuable breadth of enquiry.

